### Eligibility criteria

**
*Inclusion criteria.*
** Inclusion criteria are: infants (male or female) aged between 6–10 weeks. Infants must be exclusively breastfed with plans to continue breastfeeding through six months of age. Parents/guardians (with the participant) must reside in the study site area and be able and willing to adhere to all protocol visits and procedures. Infants must be healthy with no current illness and no chronic health problems. Informed consent must be obtained from the participants parent/guardian. Low birth weight infants (less than 2.5kg at birth) or infants born prematurely (less than 37 weeks) will be included.

**
*Exclusion criteria.*
** Exclusion criteria include formula fed infants or those whose parents/guardians are planning to use commercially available infant formula before six months of age. Infants may not have acute illness, however, once acute illness is resolved, participants may be re-revaluated for eligibility. Infants with fever (a body temperature greater than 37.5°C or mother report of fever) within three days prior to randomisation will be excluded (once fever/acute illness is resolved, participant may be re-revaluated for eligibility). Infants of parents/guardians unwilling for their infant to avoid the ingestion of supplements or herbal/other traditional medications during the study period will be excluded. Infants with any history of, or evidence for, a chronic clinically significant disorder or disease (including, but not limited to, immunodeficiency, autoimmunity, congenital abnormality, bleeding disorder, and pulmonary, cardiovascular, metabolic, neurologic, renal, or hepatic disease), self-reported history suggestive of meningitis, seizures, Guillain-Barré syndrome, or other neurological disorders, or any condition that in the opinion of the investigator may compromise the safety or well-being of the participant or compromise adherence to protocol procedures, will be excluded.

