### Follow up

The final study visit will be on Day 99 after 98 days of supplementation. Procedures for blood and faecal collections and storage and anthropomentry will be as per baseline. 

An early termination visit may occur because of a participant’s voluntary withdrawal, trial team decision, or at the discretion of the DSMB. Apart from the safety evaluations, no other evaluations required for the final study visit will be done.

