### Outcomes

*Primary:* Serum iron concentration on Day 99, after 98 days of iron supplementation and a one day wash-out period. Serum iron will be measured in venous blood collected at trial enrolment and 98 days after initiation of iron supplementation.

The primary endpoint is serum iron concentration at Day 99.

Secondary endpoints relating to iron status (all at Day 99) are:

a) Haemoglobin concentration.b) Percentage of infants with anaemia (defined as: haemoglobin < 110 g/L).c) Percentage of infants with iron deficiency anaemia (defined as: haemoglobin < 110 g/L, soluble transferrin receptor /logferritin ratio < 2.0, and ferritin < 12 ug/L or < 30 ug/L in the presence of inflammation).d) Hepcidin concentration. e) Reticulocyte number. f) Erythropoietin concentration.g) Erythroferrone concentration.

The secondary objectives are to test whether iron supplementation at this age is safe.

Endpoints related to this objective are:

a) Maternal reports of illness.b) Adverse events.c) Serious adverse events.d) Changes in gut pathogens and microbiota during the study period.e) Markers of environmental enteric dysfunction (EED).

The study will also assess potential impacts on growth, breastfeeding and feacal iron losses:

Endpoints related to these objectives are:

a) Anthropometric Z-scores relative to the World Health Organization (WHO) Growth Reference.b) Duration of exclusive breastfeeding.c) Faecal haemoglobin and iron. 

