### Statistical analysis

**
*Main study.*
** Statistical analyses will be performed using R studio and STATA software. Intervention groups will be described using conventional summary statistics (e.g., means or counts with standard deviations, medians with 25- and 75-centiles). The primary analysis concerns the effect of intervention on serum iron concentration at Day 99 (i.e., 98 days of intervention with a 1-day wash-out period after administration of the last supplement, assuming that a transient increase in serum iron concentration following iron supplementation will disappear within this period), adjusted for serum iron concentration measured at baseline. Continuous outcomes will be analysed by linear regression, with transformation of the outcome as needed to normalise the distribution of residuals. Analysis will be by modified intention-to-treat, i.e., all infants who were randomised and who received at least one supplemental dose will be included. We also plan to perform per protocol analysis (i.e., to assess the efficacy that can be attained under controlled conditions) to determine the sensitivity of our modified intention-to-treat analysis. To account for missing data, we will use multiple imputations. In secondary analyses, we will adjust for any group imbalances that may occur in prognostic variables measured at baseline. Serum iron concentrations are known to undergo diurnal fluctuation and they are known to be reduced in inflammation
^
18
^. Thus, to account for these effects, we will also conduct secondary analyses with adjustment for the time of blood collection and for plasma concentrations of C-reactive protein and alpha-1 acid glycoprotein at the time of blood collection.

Group differences in adverse events will be analysed using negative binomial regression. In this analysis, we will count adverse events as the number of days with adverse events divided by the total number of days that the infant was observed during the intervention period. In the analysis of diarrhoea, we will count an event if the parent/guardian reported three or more fluid stools (as indicated by a WHO stool chart) in the previous 24-hour recall period
^
19
^. To produce conservative effect estimates, analyses of adverse events will be per protocol.

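### The adverse-event outcome is written as a fraction of days for a count model with no offset; read literally, this makes the standard error of the rate ratio about 3 to 4 times too wide

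*Protocol article*

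**What the plan says.** **Adverse events.** The Statistical analysis section (Main study) states: "Group differences in adverse events will be analysed using negative binomial regression". The next sentence begins by referring to this same analysis and says that it will "count adverse events as the number of days with adverse events divided by the total number of days" for which the infant was observed during the intervention period. No offset, exposure term or type of standard error is mentioned. The analysis set is also fixed: "To produce conservative effect estimates, analyses of adverse events will be per protocol". Under Outcomes, adverse events and serious adverse events are listed as endpoints for the safety objective: "The secondary objectives are to test whether iron supplementation at this age is safe".

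**Breastfeeding.** Under Outcomes, "Duration of exclusive breastfeeding" is an endpoint, grouped with growth and faecal iron and apart from the safety endpoints. No sentence names a model for it. The one general rule that could reach it is "Continuous outcomes will be analysed by linear regression, with transformation of the outcome as needed to normalise the distribution of residuals". At entry (Eligibility criteria), "Infants must be exclusively breastfed with plans to continue breastfeeding through six months of age", at an age of 6 to 10 weeks. Under Follow up: "The final study visit will be on Day 99 after 98 days of supplementation". Feeding is recorded by weekly questionnaire (Data and safety monitoring).

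**The concern.** Negative binomial regression is a model for integer counts. Unequal observation time normally enters as an offset: the count stays on the left-hand side and log(days) goes on the right with its coefficient fixed at 1. The article instead defines the quantity for this analysis as the quotient itself.

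If an analyst enters that quotient as the dependent variable, the model assumes a variance of mu + alpha × mu², which is never less than mu. A fraction of days with mean 0.05 or 0.10 varies far less between infants than that. The dispersion estimate then falls to its lower limit and the standard error stays at the Poisson value for a tiny count. The quotient also discards how long each infant was observed.

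The Discussion sets out to show a gain in serum iron without extra adverse effects and without undermining exclusive breastfeeding. A statement of no excess harm is worth only as much as the analysis's ability to see an excess.

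**Working it through.** The article gives no power, event rate or dispersion for adverse events, so there is no stated figure to reproduce here. The trial's 100 infants were sized for serum iron, and this point does not touch that figure.

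**Inputs.** From the article: 100 infants allocated 1:1 (50 per arm) and 98 days of supplementation. Assumed: 5 or 10 event days per placebo infant, rate ratio 1.7, negative binomial dispersion 0.85, two-sided 5% test.

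**Standard error on the quotient.** With dispersion at its limit, SE = sqrt(1/S0 + 1/S1), where S0 and S1 are the sums of the fractions in each arm.
- 5 event days: S0 = 50 × 5/98 = 2.55; S1 = 1.7 × 2.55 = 4.34; SE = sqrt(1/2.55 + 1/4.34) = 0.79.
- 10 event days: S0 = 5.10; S1 = 8.67; SE = sqrt(1/5.10 + 1/8.67) = 0.56.

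**Standard error on counts with an offset.** SE = sqrt[(1/m0 + 0.85)/50 + (1/m1 + 0.85)/50], where m0 and m1 are the mean event days.
- m0 = 5, m1 = 8.5: sqrt(0.0210 + 0.0194) = 0.20.
- m0 = 10, m1 = 17: sqrt(0.0190 + 0.0182) = 0.19.

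The ratios are 0.789/0.201 = 3.9 and 0.558/0.193 = 2.9.

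**Power.** ln(1.7) = 0.531. With the offset the expected z is 0.531/0.201 = 2.64 or 0.531/0.193 = 2.75, giving power of 75% or 79%. On the quotient the expected z is only 0.67 or 0.95. The estimate itself still varies with a standard deviation of about 0.20. Holding the quotient's SE fixed, significance needs an observed rate ratio near exp(1.96 × 0.789) = 4.7 or exp(1.96 × 0.558) = 3.0, which is almost never seen when the truth is 1.7.

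**Simulation under these assumptions** (1,000 runs per setting, 10% of infants with shortened observation):

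| Placebo event days | Model | Mean log ratio | SE | Power |
|---|---|---|---|---|
| 5 | Count + offset | 0.53 | 0.20 | 78% |
| 5 | Quotient, model SE | 0.53 | 0.80 | 0% |
| 5 | Quotient, robust SE | 0.53 | – | 78% |
| 10 | Count + offset | 0.53 | 0.19 | 79% |
| 10 | Quotient, model SE | 0.53 | 0.56 | 0% |
| 10 | Quotient, robust SE | 0.53 | – | 79% |

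**A second simulation with other assumptions** (rate ratio 2.0, placebo event days 2%, 5% or 15% of days, dispersion 1, 400 runs) gave power of 82%, 92% and 89% with the offset, 0%, 0% and 7.5% on the quotient with model-based SE, and 83%, 91% and 90% with robust SE. With no true effect, rejection was 4 to 9% with the offset, 6 to 10% with robust SE on the quotient, and 0% on the quotient with model-based SE.

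**Breastfeeding.** 98 days is 14 weeks, so the final visit falls at 6 + 14 = 20 to 10 + 14 = 24 weeks of age, before six months. An infant still exclusively breastfed then has an unfinished duration. Assuming a constant hazard of stopping, a hazard ratio of 2, 50 per arm, weekly recording and 10% early loss (2,000 runs):

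| Placebo infants still exclusive at day 98 | Linear regression | Log-rank | Loss (points) |
|---|---|---|---|
| 90% | 13.7% | 24.6% | 10.9 |
| 70% | 40.1% | 55.7% | 15.6 |
| 50% | 63.2% | 74.2% | 11.0 |
| 30% | 80.2% | 85.9% | 5.7 |

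Type I error was 4.8 to 6.0% for both methods. The observed mean difference was smaller than the uncensored one (for example −15.7 against −70.7 days at 50% retention). The uncensored figure extrapolates the constant hazard beyond follow-up, so only its direction should be used.

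**The case against.** Event days over days observed is the ordinary definition of an incidence rate, and negative binomial regression with an exposure term is the usual model for one. The sentence may be loose wording for exactly that, and an article can leave the offset to the analysis plan, which is not shown. This reading is plausible and stands as a possibility. However, the article states what is counted in this named analysis and mentions no exposure term, so the literal reading is open to whoever writes the code.

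The severe loss of power also needs three things together: the quotient as outcome, a 0-to-1 scale and model-based standard errors. With robust standard errors, or with the rate expressed per 100 days, it disappears (71% and 81% power in a 300-run check of the per-100-day version under the same assumptions). That is correct and limits the point.

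A reader might infer that the adverse-event model is biased towards no effect. It is not: the point estimate is the same under every version, and only the interval is wrong. A reader might also infer that very briefly observed infants will distort the result. The per-protocol set would probably leave out most of them, although the article does not define that set closely.

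On breastfeeding, a reader might infer that the plan commits a second safety outcome to an invalid model. The documents do not support this. The endpoint is not on the safety list, no model is named for it, and linear regression reaches it only through the general rule. The entry criterion asks for plans to continue breastfeeding, not exclusive breastfeeding, so the censored share is unknown. With nearly equal follow-up, linear regression roughly compares restricted means and keeps its type I error.

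**Conclusion.** The point holds for adverse events in a limited form. The outcome as worded does not fit the model named for it. If followed literally with model-based standard errors, the rate ratio keeps its value but its standard error is about 3 to 4 times too wide, and power for a rate ratio of 1.7 falls from about 75 to 80% to about 0%. These sizes rest on assumed event rates and dispersion, none of which the article gives, and on the literal reading. The direction does not depend on them while event days remain a small fraction of days observed.

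The breastfeeding point is secondary and conditional. If the general rule is applied, the cost is about 6 to 16 percentage points of power under the assumed stopping rates, plus an understated difference; the test itself stays valid.

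**What to change.** In the Statistical analysis section or the analysis plan, state that the adverse-event outcome is the integer number of event days per infant, modelled by negative binomial regression with log(days observed) as the offset, and that the result is reported as a rate ratio with its 95% confidence interval.

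Name a model for duration of exclusive breastfeeding: time from randomisation to the first other food or fluid, censored at the last weekly questionnaire, compared by log-rank test or Cox regression.

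Both changes are wording and code. The daily health records and weekly feeding questionnaires already planned supply the data, so nothing further needs to be collected.

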### Study objectives

The primary objective is to measure the impact of daily iron supplements for 98 days starting at 6–10 weeks of age on serum iron concentration at the end of the intervention in breastfed Gambian infants. The secondary objectives are to determine if iron supplementation at this age will affect: (1) the duration of exclusive breastfeeding, (2) growth, (3) pathological processes in the gut, and (4) the frequency of adverse events.

Additionally, a qualitative study will assess the acceptability of the iron supplementation efficacy trial. The supplementary objectives are to:

a) Explore mothers’ (the main care providers) perspectives on the acceptability of iron supplementation in their young, breast-fed infants through in-depth interviews.b) Explore the acceptability of iron supplementation in young, breast-fed infants through focus group discussions with local stakeholders.c) To integrate the quantitative and qualitative clinical intervention outcomes to explore the acceptability of iron supplementation in young, breast-fed infants.

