### Baseline

Once parents/guardians of the infant have signed the informed consent document, the infants will be physically examined by a study nurse and, if the infant is considered as generally healthy, their height and weight will be measured. At baseline, a 3 ml blood sample will be collected (0.5 ml in EDTA tube and 2.5 ml in serum tube) to assess the full blood count (including reticulocyte count) and to determine iron status. Parents/guardians of participants will be asked to place nappies inside-out on participants the morning before the baseline or endline visits. Faecal samples will be collected from the nappies by field workers using a spatula. This will be put in universal containers and kept in a cold box. Both blood and stool samples will be transported to the Keneba laboratory for processing and storage into -80°C within 4hrs after collection. Participants who do not pass stool will be provided with labelled universal containers and a cold box to collect faecal samples. The sample will be transported and processed by the field supervisor. This will be stored immediately into a −20°C freezer in Jarra Soma. Frozen stool sample will be transported and stored in Keneba at −80°C. Infants with haemoglobin concentration < 70 g/L will be referred to the regional health centre for treatment according to national guidelines. For safety purposes, all infant’s health will be monitored by the field workers for two weeks post supplementation. See
Figure 2 for the full study scheme.

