### Interventions

Supplements will be administered as drops from a liquid formulation containing either iron (7.5mg contained in 0.5mL) or its placebo (sorbitol solution USP 70%, an inactive ingredient in the iron supplements). The intervention and placebo will be issued in identical dark brown plastic bottles. The ferrous sulphate (intervention) and sorbitol (placebo) will be manufactured such that they are identical in terms of taste and appearance thus, allowing robust allocation concealment. Infants will be visited in their homes daily for 98 days by the field workers who will administer the drops. Products will be stored at ambient temperature (15–30˚C), away from direct sunlight, at both the MRCG@LSHTM Keneba Field Station main store and Jarra Soma health clinic in a locked room. The procured products have a 12-month shelf-life and expiry dates will be checked by the sub-investigator during study implementation.

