**In-depth interviews with infants’ mothers**

The in-depth interviews will discuss the acceptability of iron supplementation in infancy from the perspective of mothers, but data obtained from the focus group discussions will be used to finalize the interview schedules. Using these interview schedules, 30–60-minute individual in-depth interviews will be conducted with mothers whose infants are enrolled in the trial. Interviews will be conducted, in Mandinka, by a qualitatively trained, female member of the study team, and will be audio recorded. In-depth interviews will employ concurrent and retrospective data collection by interviewing mothers during the last four weeks of the trial and in the two-week follow-up window. The location will be chosen by the interviewee to add comfort and will most likely include the homes of participants and within local villages. Data will be collected towards the end of the infant’s enrolment so that mothers have had mostly the full experience until that point.

All answers obtained and information given through both focus group discussions and in-depth interviews will be anonymised, collated, and analysed. NVivo (2020 release) software will be used to analyse qualitative data. 

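### The only between-arm adverse-event regression described covers the intervention period, so the two weeks of safety follow-up planned for every infant do not enter it

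*Protocol article*

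**What the plan says.** Three parts of the protocol article bear on the time window.

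- **Data collection.** The Baseline section says, giving safety as the reason, that "all infant’s health will be monitored by the field workers for two weeks post supplementation". The section on in-depth interviews confirms the arrangement when it plans "interviewing mothers during the last four weeks of the trial and in the two-week follow-up window".
- **Analysis.** The Statistical analysis section states: "Group differences in adverse events will be analysed using negative binomial regression". The measure is then fixed as "the number of days with adverse events divided by the total number of days that the infant was observed during the intervention period". The intervention lasts 98 days throughout the article; the Interventions section says "Infants will be visited in their homes daily for 98 days by the field workers who will administer the drops".
- **Objectives and endpoints.** Study objectives names "the frequency of adverse events" among the things iron might affect. The Outcomes section lists maternal reports of illness, adverse events and serious adverse events as safety endpoints and gives none of them a time limit.

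No modelled or tabulated comparison of the two follow-up weeks is described.

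**The concern.** The article plans safety follow-up beyond the last dose, then chooses an analysis window that stops before it. This is not a detail left open for a later document: the window is stated, and it is narrower than both the data collection and the safety endpoints.

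The choice of measure sharpens the effect. The regression counts days with adverse events, not onsets, so a cut-off at Day 98 shortens every episode still running and ignores every episode that starts afterwards. If iron led to illness that appears or persists just after dosing, the regression could not show it. Safety matters to the trial's purpose: the Discussion says the aim is to raise serum iron without added adverse effects, and the trial is meant to inform a larger one. With 100 infants, safety information is scarce.

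**Working it through.** The article gives no adverse-event figure to reproduce. Its sample size rests on serum iron and is not affected by this point.

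**Inputs**

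- Supplementation: 98 days (Interventions).
- Safety follow-up: two weeks, or 14 days, for all infants (Baseline).
- Infants: 100 (Sample size).
- Adverse-event rate: not given, so a range is assumed below.

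**1. Share of monitored time outside the regression**

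- Per infant: 98 + 14 = 112 days, and 14 / 112 = 12.5%.
- All infants, with complete follow-up: 100 × 14 = 1,400 of 100 × 112 = 11,200 infant-days.

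These are ceilings. Daily visits are promised only for the 98 days, and the article does not say how often infants are seen afterwards.

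**2. How single episodes are counted**

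- Onset on Day 97: Days 97 and 98 count, giving two days whatever the length of the illness.
- Onset on Day 100: no days count.

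**3. How many event days could be involved**

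Assume between 0.001 and 0.02 adverse-event days per infant-day, at the same rate in both periods.

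- Follow-up: 1,400 × 0.001 = 1.4, up to 1,400 × 0.02 = 28 event days.
- Intervention period: 9,800 × 0.001 = 9.8, up to 9,800 × 0.02 = 196 event days.

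**4. What pooling the two periods would do to a rate ratio**

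Assume equal background rates per day, a rate ratio of 1.50 during dosing and 1.00 afterwards.

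- Pooled ratio: (98 × 1.50 + 14 × 1.00) / 112 = 161 / 112 = 1.44.

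Pooling dilutes a purely on-dose effect slightly. The planned regression returns 1.50 whatever happens in follow-up, so it carries no information about those weeks.

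**5. Numerator and denominator must match**

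If follow-up events were counted but follow-up days were not, and background rates were equal, the rate would be inflated by up to 112 / 98 = 1.14.

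**6. What the intervention period means for an infant who stops early**

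The Sample size section speaks of infants ceasing supplements partway through the intervention period. On that usage the period runs on after an infant stops, and it is the scheduled 98 days. Days after stopping but within the 98 can therefore still count, provided the infant is observed.

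**The case against.** **Other safety review exists.** A reader might infer that events in the follow-up weeks are never compared between arms. The article does not support that. Under Data and safety monitoring, the DSMB sees safety data tabulated by coded arm in closed session, with no restriction to the supplementation period. The restriction applies to the regression. This objection stands, but a monitoring review is not the trial's reported safety estimate.

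**Early stoppers.** A reader might also infer that observation after an infant stops supplements is lost under the stated window. Step 6 of the working shows otherwise. Any loss of those infants would come from a different sentence, "To produce conservative effect estimates, analyses of adverse events will be per protocol", which concerns the analysis set and not the window.

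**An on-treatment window is a recognised choice.** Restricting the model to the period of daily visits keeps ascertainment uniform. Adding weeks with perhaps less frequent contact mixes two intensities of observation in one rate and can pull a real on-dose effect toward the null. This stands as a reason to keep the intervention-period regression as the main analysis. It does not justify leaving the follow-up weeks uncompared: within those weeks the article plans the same monitoring for both arms, under blinding, so a separate comparison by arm is fair.

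**No harm is shown.** The cut-off applies equally to both arms, and the article gives no rate from which a bias could be derived. That is correct, and it limits the size of the point.

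**A fuller document may add the tabulation.** It may, and the mere absence of a table would not be a finding. The point rests on the window that the article does state.

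**Conclusion.** The point holds for the regression described in the Statistical analysis section. Safety follow-up planned for all infants falls outside that comparison by a stated rule, and episodes running at Day 98 are cut short, although the safety endpoints carry no such limit.

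The excluded share is at most 12.5% of monitored days. That assumes complete follow-up of 14 days and a 98-day intervention period. The effect on the estimated rate ratio is unknown in both size and direction, because no adverse-event rates are given. The event-day counts in the working are illustrations over an assumed range.

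The conclusion does not extend to the DSMB's review or to days after early stopping within the 98 days. It does not touch the primary endpoint or the sample size. It is a modest gap in the safety analysis that can be closed with planned data.

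**What to change.** In the Statistical analysis section:

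1. Keep the intervention-period regression as the main adverse-event analysis. State that the intervention period is the scheduled 98 days, whether or not an infant stops supplements early.
2. Add a comparison by arm of adverse events and serious adverse events over the two-week follow-up. State how often infants are contacted in those weeks.
3. Add a supplementary analysis from first dose to the end of follow-up, on the same calendar window for every infant so that its length does not depend on adherence. Restrict both event days and the denominator to days actually observed.

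The cost is some added wording, one more model run and a tabulation. No new visits are needed if the planned monitoring records illness in a usable form, which the article does not spell out. The drawbacks are slight dilution of a purely on-dose effect in the supplementary analysis (1.50 to about 1.44 under the stated assumptions) and possibly less intensive ascertainment after Day 98. Both are reasons to keep the 98-day analysis as the main one and to report the follow-up separately.
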